**Fig. 2 Fig2:**
[figure not shown]
Time schedule of recruitment, intervention and assessments (SPIRIT) Legend: *t* indicates when the event occurs during the intervention. If unspecified, it applies to both rounds; if absent, the event occurs pre-intervention

### The structure of the intervention

The NBHIs are structured as group-based programmes delivered over 10 consecutive weeks, with one weekly session. The interventions will be delivered between March and November 2025. The intervention will be rolled out in two consecutive rounds, each involving between two and three groups at each site. Each group consists of 8 to 12 participants in a closed group. The closed group format, where the participants attend the same group for the full duration of the programme, is intended to provide participation continuity and to support the development of trusting relationships and psychological safety. Sessions held in the municipality centres have a duration of two and a half hours, while those at the outpatient clinic have a duration of one and a half hours. 

### Study setting

The intervention will be carried out as an interdisciplinary initiative facilitated by two health professionals at each site, who already have experience in delivering NBHIs to the target group. The Nature Impact Feasibility Study will be conducted at municipality centres in Kolding, in the Region of Southern Denmark, and Silkeborg, in the Central Denmark Region, and at an outpatient clinic in Glostrup, in the Capital Region of Denmark. The intervention conducted in Silkeborg will take place at two different natural environments. The sites are further described in Table 2. Across the three sites, contextual conditions are expected to vary, including differences in physical environments (e.g., urban versus more secluded natural settings), organisational structures and participant characteristics. These contextual variations are considered a central point of focus in the intervention, as they may influence both the implementation and the feasibility. To explore this, contextual factors will be systematically examined through qualitative and quantitative data sources, allowing for an analysis of how context shapes intervention delivery and feasibility outcomes across sites.

**Table 2 Tab2:** Characteristics of the included sites

Location	Natural environment	Facilities
Silkeborg 1 Municipality	-Urban-adjacent forest with a lake -Bonfire area -Open lawn -Located near a folk high school -Publicly accessible and is used by the nearby folk high school -Light noise from highway	-Seat pads-Toilets
Silkeborg 2 Municipality	-Large hilly deciduous forest -Bonfire area -Open clearing -Publicly accessible and is used by school classes -No noise from traffic	- Seat pads -Warm water for drinks -Toilets
Kolding Municipality	-Hilly deciduous forest near a stream -Bonfire area -Located in a therapy garden -Only publicly accessible via agreements -No noise from traffic	-Seat pads -Snow suits -Warm water for drinks -Toilets
Glostrup Region	-Urban forest with a mix of deciduous and evergreen trees -Open clearing -Located near the outpatient clinic -Considerable noise from traffic and building sites	-Raincoats -Toilets in the nearby outpatient clinic

The research team will have continuous communication with the health professionals, to facilitate ongoing professional exchange and collaboration.

### Recruitment in the Nature Impact Feasibility Study

In the Nature Impact Feasibility Study, two distinct participant groups are recruited: (1) health professionals and (2) individuals experiencing mild to moderate anxiety, depression and/or stress, hereafter referred to as participants. The health professionals are working in the municipality centres in Kolding or Silkeborg or at the outpatient clinic in Glostrup.

Participants will first be approached through municipal centres, general practitioners, job centres, self-referral or the outpatient psychiatric clinic. Following this outreach, the health professionals delivering the interventions are responsible for identifying eligible participants, conducting screenings and delivering the intervention.

Inclusion criteria for participants include being 18 years or older, experiencing symptoms of mild to moderate anxiety, depression and/or stress that significantly affect daily functioning and having sufficient proficiency in Danish. Being on sick leave is not a requirement for participation. Exclusion criteria include having significantly reduced functional capacity, being unable to walk one kilometre, exhibiting suicidal ideation and/or experiencing substance abuse issues.

### Sample size justification in the Nature Impact Feasibility Study

As this study is designed to assess feasibility and implementation rather than intervention effectiveness, no formal statistical power calculation was performed [12, 15, 16]. The target sample size of 120 participants, distributed across three implementation sites, was determined to provide sufficient information on key feasibility and implementation outcomes, including reach, dose, fidelity, adaptations, acceptability, mechanisms of change and contextual factors influencing implementation. A sample of this size is expected to provide adequate variation in participant experiences and implementation processes across sites, enabling meaningful assessment of the feasibility of recruitment procedures, intervention delivery, data collection methods and implementation outcomes. The sample size was also considered appropriate to inform the design and planning of a subsequent larger-scale evaluation. This approach is consistent with recommendations that the design, including sample sizes, in feasibility studies should be justified in relation to feasibility objectives rather than statistical power for effectiveness testing [15, 16].

### Data sources

Six complementary data sources will be used to assess feasibility outcomes and to explore the appropriateness of outcome measures and the intervention’s potential to produce meaningful effects.

Data collection methods followed by data analysis procedures are summarised below, with each data source mapped to specific feasibility parameters following the CONSORT extension to pilot and feasibility studies [15]. The time schedule of enrolment and the assessments collected are displayed in Fig. 2.

#### Participant observations

Participant observations will be conducted during the interventions, with two observations per site in the first intervention round and one observation per site in the second intervention round. All observations cover a full session. The observations follow a participant observation approach inspired by James Spradley [17] and systematic field notes will be taken.

The observations will be carried out by a single trained researcher, who will participate in the sessions while maintaining a low degree of involvement. The use of systematic field notes, supported by an observation template, will ensure consistent attention to contextual elements such as group dynamics and therapeutic adaptations.

#### Focus group interviews

Semi-structured focus group interviews will be conducted with participants and health professionals separately. Separate interview guides will be developed for participants and health professionals, focusing on the overall feasibility objectives of the study, ensuring a consistent exploration of key aspects such as the implementation process, the participants’ and healthcare professionals’ experiences and contextual factors, while allowing for flexibility to raise unanticipated perspectives. The focus group interviews with the participants will be conducted after completion of the first intervention period whilst the focus group interviews with the health professionals will be conducted mid-intervention in the second round of interventions at each site. In total six focus group interviews will be conducted with the participants, and three focus group interviews will be conducted with the health professionals. The interviews are conducted by two researchers, a lead and a co-interviewer. All interviews will be audio recorded and transcribed verbatim.

Focus group interviews are selected due to their capacity to support with rich and diverse data created through social negotiations in group discussions [18]. The focus group interviews are particularly suited for examining feasibility parameters, as they allow for exchange and reflection among participants, which through the social interactions allow for broader perspectives, compared to individual interviews, enhancing understanding of the intervention’s acceptability and implementation process.

#### Participant registration forms

Prior to the start of the intervention, health professionals will complete a registration form for each referred participant, capturing information on participants’ entry/referral into the intervention and, if applicable, the reason for declining. The form includes open-text fields for the health professionals to fill out.

#### Participant questionnaires

Participants will be invited to complete two questionnaires assessing their mental health status and their relationship to nature using the validated instruments; WHO-5 Well-Being Index [19], Depression, Anxiety and Stress Scale (DASS-21) [20], Satisfaction with Life Scale (SWLS) [21] and Environmental Identity Scale [22]. These questionnaires are filled out pre- and post-intervention, right before the beginning of the first and at the end of the 10th session.

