#### Quantitative data analysis

Quantitative data will primarily be derived from participant questionnaires and structured elements of the participant and the intervention registration forms.

The participant questionnaires will be analysed using descriptive statistics to inform the feasibility parameters dose and reach as well as secondary outcome measures related to changes in participants’ mental health and their relationship to nature as well as the relevance of the chosen mental health outcome measures. Descriptive analyses will include measures of central tendency and distribution, e.g. means, medians, standard deviations, for each timepoint, alongside pre and post comparisons to examine a potential change.

Data from the participant registration forms will be analysed descriptively to assess referral sources and reasons for non-participation, thereby informing the feasibility parameter reach.

Data from the intervention registration forms will be analysed descriptively to assess information on the feasibility parameters, fidelity and adaptations as well as mechanisms of change.

All the data will inform contextual factors.

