### Ethical considerations

All participants will receive both oral and written information about the purpose of the Nature Impact Feasibility Study, the intervention procedures and their rights as research participants. As part of the informed consent process, participants are informed about applicable data protection regulations (GDPR) and provided with contact information for the data controller.

Written informed consent is obtained from all participants prior to the initiation of any study procedures. After providing consent, participants are granted access to the participant questionnaires via a QR code, which directs them to a secure digital data collection platform. All interview recordings will be deleted following transcription, and the resulting transcripts will be pseudo-anonymised to prevent any statements from being linked to individual participants.

All data will be handled confidentially and will be stored on secure, access-restricted systems. Each participant is assigned a unique code that allows their responses to be linked across different time points (e.g. from baseline to post-intervention), without the possibility of re-identification. No key exists that could link these codes to personal identities. At the conclusion of the study, all data will be stored and, where appropriate, archived in accordance with institutional guidelines for data security and research integrity.

Moreover, the Nature Impact Feasibility Study is registered on ClinicalTrials.gov (NCT06981000) and has received exemption from Danish Research Ethics Committees (no. F-25008378).

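### The only stated post-intervention collection point is the end of session 10, so pre–post change and dose would describe mainly the participants who stayed

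*Protocol article*

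**What the plan says.** All places are in the protocol article.

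- **Timing.** Under Participant questionnaires, the WHO-5, DASS-21, SWLS and Environmental Identity Scale are completed "right before the beginning of the first and at the end of the 10th session". No other post-intervention occasion is described.
- **Analysis.** Under Quantitative data analysis, the questionnaires are summarised by "means, medians, standard deviations, for each timepoint, alongside pre and post comparisons to examine a potential change". The text does not say which participants enter the comparison or whether it is paired.
- **Access and linkage.** Under Ethical considerations, "participants are granted access to the participant questionnaires via a QR code, which directs them to a secure digital data collection platform". The same section says "Each participant is assigned a unique code that allows their responses to be linked across different time points", and then "No key exists that could link these codes to personal identities".
- **Use.** The secondary aim is to explore change in mental health, to judge the suitability of the measures and to give some insight into potential efficacy. The Discussion (Expected contributions) repeats the efficacy purpose.
- **Dose and dropout.** Table 1 names the post-intervention questionnaire as the only source for the share of sessions attended. For dropout and its reasons it lists participant questionnaires beside interviews with health professionals.
- **Expected losses.** In Table 3, retention of 70–89% is Amend. Completion of outcome measures is Go at 80% or more and Amend at 70–79%.

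**The concern.** The design has one arm, so no comparison group shares the attrition and offsets it. Whoever supplies a post form determines what the change describes. If the form is offered only as session 10 closes, people who stopped earlier or were away that day drop out of the result, and they may well differ from the rest both in starting severity and in how they fared.

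Two things are at stake. One is the signal on potential efficacy and on the outcome measures, which is meant to inform a later effect study. The other is dose, which belongs to the primary feasibility aim. People who left early attended fewer sessions, and they are the ones least likely to be there to report it.

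**Working it through.** The plan gives no change, SD or attrition figure to reproduce, and 120 is not derived from a formula. The check is therefore algebra with stated assumptions.

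**Inputs from the article.** Target of 120 participants (Sample size justification); response levels of 70%, 80% and 90%, taken from the thresholds in Table 3. Reading these as the share of participants with a post form is an assumption.

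**Assumed inputs.** The baseline gap and the change gap between responders and non-responders. The article gives neither.

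**Counts.** 120 × 0.70 = 84 post forms (36 missing); 120 × 0.80 = 96 (24 missing); 120 × 0.90 = 108 (12 missing).

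**Step 1: unpaired timepoint means.** Let r be the share with a post form, B the baseline mean, P the post mean, and subscripts R and N responders and non-responders, scored so that higher is better.

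P_R − [r·B_R + (1 − r)·B_N] = (P_R − B_R) + (1 − r)·(B_R − B_N)

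The first term is the responders' own change. The second is composition bias: share missing × baseline gap.

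| Assumed gap, B_R − B_N | r = 0.70 | r = 0.80 | r = 0.90 |
|---|---|---|---|
| 0.8 SD | 0.24 | 0.16 | 0.08 |
| 0.5 SD | 0.15 | 0.10 | 0.05 |
| 0.2 SD | 0.06 | 0.04 | 0.02 |
| 0 | 0 | 0 | 0 |
| −0.5 SD | −0.15 | −0.10 | −0.05 |

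A positive gap means that those without a post form started worse, and improvement is overstated. A negative gap means that they started better, and improvement is understated.

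**Step 2: linked pairs.** Using post minus pre in the same people, the composition term is 0 at every response level.

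**Step 3: what pairing leaves.** With C for mean change, the mean over all enrolled is r·C_R + (1 − r)·C_N, so

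C_R − C_all = (1 − r)·(C_R − C_N)

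If non-responders are assumed to improve 0.5 SD less, this is 0.30 × 0.5 = 0.15 SD, 0.20 × 0.5 = 0.10 SD and 0.10 × 0.5 = 0.05 SD at 70%, 80% and 90% response. With no difference in change it is 0. Pairing alone does not touch this term; only post forms from more of the non-attenders reduce it.

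**Step 4: dose.** Anyone who left before session 10 attended at most 9 of 10 sessions. With the post form as sole source, these people supply no attendance figure. The reported share is then likely to be too high, though by how much cannot be said from the article. For the same reason the post form can say little about why people left; the interviews with health professionals remain as the other source on that question.

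**The case against.** The strongest reply is that the article can be read as already planning a sound comparison. A reader might infer that everyone at baseline is set against completers at the end, and that the change must therefore look too good. The documents do not support that.

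- The pre–post comparison is named separately from the per-timepoint summaries, and the linking code makes a paired analysis possible and probably intended. Composition bias is then 0 SD. **This stands**, and the figures in Step 1 apply only if the comparison is unpaired.
- The direction depends on who leaves, and the article gives no gap. **This stands**; the sign can reverse.
- Physical presence is not stated as a condition; it is a reading of the timing. **This stands** too, but no other occasion or route is described.
- One might also infer that codes will be lost over ten weeks and pairs broken. The article says that codes are assigned and does not say that participants must remember them, so this is speculation.
- Analysis sets and missing-data methods commonly sit in a full protocol or SAP that is not shown. **This stands**, and their absence is not the point here. A mixed model would be a preference in a descriptive one-arm study.
- Change is a secondary, exploratory aim. No progression criterion uses its size, and Table 3 counts missing forms as a feasibility result. **This stands**, and it limits the importance of the point.

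What the reply does not answer is the stated collection moment itself. Selection on response remains after pairing, and dose is part of the primary aim.

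**Conclusion.** The point holds in a limited form. As written, the plan seeks the post form at one moment, with no stated route for those who withdrew or were absent, so change and dose would describe mainly those who stayed.

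For change, selection on response amounts to 0.05–0.15 SD at 90–70% response under an assumed 0.5 SD difference in improvement, and to nothing if there is no such difference. If the comparison turned out to be unpaired, a composition term would be added: 0.10 SD at 20% missing and an assumed 0.5 SD gap, and of either sign. All gaps are assumptions. For dose, overstatement is likely but cannot be sized.

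The Go/Amend/Stop decision does not use the size of the change, so that decision is not affected through it. The procedure should still be changed, because the result is meant to inform the next trial and the remedy costs little.

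**What to change.** 1. Have each site send the same QR link at week 10 to every enrolled participant, including those who stopped attending or missed session 10, with a short window (for example 14 days). Health professionals complete a registration form for each referred participant, so sites should know whom to contact and no research key to the codes is needed. This also brings in attendance figures for people who left.
2. State that the pre–post result is within-person change in linked pairs, reported as mean, SD and 95% CI.
3. Tabulate baseline scores of those with and without a post form.
4. Word the efficacy signal as applying to responders.

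The cost is one message per site per round (3 sites × 2 rounds = 6) and one extra table. The downside is that some forms will be completed a few days later and away from the session. Delivery was planned for March to November 2025; if collection has closed, items 2 to 4 can still be done. Neither a mixed model nor a code that participants can regenerate is needed.

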#### Intervention registration forms

Throughout the intervention, health professionals will complete a session log after each session. This log records any deviations from the planned intervention content, including changes in session timing and location, alongside the reasons for these adjustments, e.g., weather conditions or participant needs and preferences.

### Data analysis

#### Qualitative data analysis

Qualitative data from transcripts from the focus group interviews and the systematic field notes from participant observations will be analysed thematically following the approach described by Braun and Clarke [23, 24]. The analysis will be supported by NVivo software to facilitate coding and the identification of patterns across data sources.

The focus group interviews will be analysed to explore the feasibility parameters reach, adaptations, acceptability, mechanism of change and contextual factors alongside perspectives on secondary outcomes, related to the mental health status of participants and the assessment tools hereof. Moreover, the interviews with the health professionals will inform the feasibility parameter fidelity.

The systematic field notes from the participant observations as well as the open-text responses from the participant registration forms and the intervention registration forms will be thematically analysed [23, 24]. This analysis will contribute to an understanding of feasibility parameters including reach, fidelity, adaptation, acceptability, mechanisms of change and contextual factors.

#### Quantitative data analysis

Quantitative data will primarily be derived from participant questionnaires and structured elements of the participant and the intervention registration forms.

The participant questionnaires will be analysed using descriptive statistics to inform the feasibility parameters dose and reach as well as secondary outcome measures related to changes in participants’ mental health and their relationship to nature as well as the relevance of the chosen mental health outcome measures. Descriptive analyses will include measures of central tendency and distribution, e.g. means, medians, standard deviations, for each timepoint, alongside pre and post comparisons to examine a potential change.

Data from the participant registration forms will be analysed descriptively to assess referral sources and reasons for non-participation, thereby informing the feasibility parameter reach.

Data from the intervention registration forms will be analysed descriptively to assess information on the feasibility parameters, fidelity and adaptations as well as mechanisms of change.

All the data will inform contextual factors.

#### Data integration

A mixed methods convergent design will be applied, whereby qualitative and quantitative data are analysed separately and integrated during the interpretation phase. The integration will be guided by a thematic alignment. This approach allows for a comparative exploration of how qualitative insights and quantitative trends converge or diverge across feasibility parameters, mechanisms of change and contextual factors.

The two types of data will be merged in a weaving structure, which enables the presentation of complementary findings within thematic categories. Integration will involve systematically comparing and linking findings from qualitative and quantitative analyses within each domain to identify areas of convergence, divergence and complementarity. This approach is displayed in Fig. 3. A theme emerging from qualitative data can guide a focused exploration of a related pattern in quantitative data. Conversely, trends from quantitative data can prompt a deeper understanding through qualitative insights [13]. Where relevant, joint displays will be used to visually present integrated results, enhancing clarity and facilitating nuanced interpretation of feasibility outcomes.

